# Study Protocol

## 1. Study Title

(Korean) Research-led, Non-randomized Cluster Clinical Trial on the Effectiveness of Home-Based Medical Care in Reducing Unscheduled Hospitalizations Within 6 Months of Enrollment Among Advanced Solid Cancer Patients Undergoing Anti-cancer Treatments

(English) A Cluster Non-randomized Controlled Trial on the Effectiveness of a Korean Model for Home-Based Care Among Patients with Advanced Cancer

## **1. The title of the clinical study**

A Cluster Non-randomized Controlled Trial on the Effectiveness of a Korean Model for Home-Based Care Among Patients with Advanced Cancer

## **2. Introduction**

### **A. Background**

#### **\* The unmet medical needs of patients with severe diseases**

Patients with advanced stage cancer prefer to spend their lives in their homes, accept the inevitable, and prepare for their death. Therefore, providing adequate medical services to meet patients' requirements are a worthwhile goal for the present medical system. Hospitalized patients are forced to give up their life values. However, they have the right to live on their own terms at their homes, receive proper treatment and care, and spend time as they wish. Thus, medical services must provide home-based medical care to fulfill the needs and wishes of patients with advanced cancer.

#### **\* A lack of medical support for patients with advanced cancer**

The HBMC and supportive care for patients with advanced cancer who live with chronic conditions often have unmet medical needs. Patients with advanced cancer often find it expensive to undergo treatment in hospitals and they do not receive the HBMC because they do not have alternatives to staying in hospitals. Furthermore, a long-term hospital stay in tertiary general hospitals reduces the number of available acute care beds, which may prevent many patients who need acute care from receiving proper treatment. Additionally, patients with advanced cancer do not have primary care physicians because they receive chemotherapy and have no choice but to visit emergency rooms (ERs) for small medical concerns, inevitably

causing overcrowding in ERs.

## **B. Literature Review**

### **○ The HBMC is cost-effective and improves the quality of life of patients staying at home**

- There is a growing need for continuous medical services with the increase in the ageing population and development of technology. Additionally, the number of patients staying at home who cannot visit medical institutions due to medical and social problems is increasing. Consequently, HBMC services have been developed and implemented for such patients.
- Unlike the existing residential facilities that concurrently provide acute-phase treatments, medical services, and care, such as long-term care hospitals and nursing homes, the HBMC encompasses the characteristics that allow the patient to stay at home and ensures visits by the medical professional at the patient's place of residence to provide medical services.
- The target and scope of the HBMC are increasingly expanding worldwide because the HBMC improves patients' quality of life because they can continue to live at home and lowers the cost because fewer medical facilities are necessary to provide services, such as buildings.

### **○ HBMC interventions for non-severely ill patients staying at home reduce the use of medical services and improve their quality of life**

- The participants of studies conducted overseas on HBMC interventions have been patients staying at home who have mobility impairments and require continuous management through primary medical institutions, such as frail older adult patients, patients with complex chronic diseases (i.e., patients with multiple chronic diseases, including dementia, severe mental illness, and diabetes), patients with mobility difficulties, or patients with disabilities.
- The effect of home-based primary care (HBPC) on the improvement of the quality of life of non-severely ill patients staying at home is well known. Continued HBMC interventions for non-severely ill patients residing at home have demonstrated a positive effect by reducing the

use of medical services and total medical costs even when followed up after 18 months.

- **HBMC interventions that incorporate transitional care are effective for severely ill patients**

- Providing the HBMC as a part of transitional care for patients with high risk for acute exacerbation, such as heart failure and chronic obstructive respiratory disease, discharged from acute-care hospitals positively reduces readmissions and medical costs.
- Providing home-based palliative care to severely ill patients with incurable illnesses, such as cancer, heart failure, and chronic obstructive respiratory disease, and limited life expectancy has been proven to effectively control their symptoms without shortening their life expectancy and improve their health-related quality of life.

### **3. The aim of the study**

This study aims to assess the effects of a home-based medical intervention program on reducing unplanned rehospitalization within 6 months by providing home visits and periodic checkups by the medical staff for patients with advanced cancer with mobility difficulties and their family caregivers.

### **4. The design of the study**

#### **A. The phase of the clinical study**

- Phase III

#### **B. Study participants**

Participants will include patients with advanced cancer with mobility difficulties and their family caregivers.

## **5. Inclusion and exclusion criteria**

Both the patient and their family caregivers must meet the following criteria to be eligible for participation in this research.

### **A. Inclusion criteria**

#### ***1) Patients***

(1) A person who has an advanced-stage solid cancer diagnosis (ICD-10 Code C00-C70) and is receiving or planning to receive cancer treatment. (2) A person who meets one of the following conditions: (a) has been evaluated as having Eastern Cooperative Oncology Group (ECOG) performance status 2 or (b) has been evaluated as having ECOG performance status 1 and is aged above 65 years. (3) A person who wishes to stay at home (In South Korea, patients who need supportive care are usually hospitalized in long-term care hospitals due to the national insurance coverage and the lack of supportive care in cancer treatment hospitals. (4) A person who has a family caregiver *cohabiting with them or visiting their home three or more times per week*. (5) A person who wishes to participate in the research.

#### ***2) Caregivers***

The following are the inclusion criteria for family caregivers. (1) A family member of the patient (“family” refers to the patient’s spouse [including a common-law partner], children and their spouses, siblings and their spouses, and close relatives and their spouses). (2) A person who meets one of the following conditions: (a) lives with the patient (patient’s household member), (b) does not live with the patient, but visits the patient’s home more than three times per week, (c) wants the patient to stay at home, (d) can communicate with the medical staff via telephone without any difficulties, or (e) wishes to participate in the research.

### **B. Exclusion criteria**

#### ***1) Patients***

Patients will be excluded from the study if they (1) cannot speak, understand, or read Korean,

(2) are judged by a medical doctor to be unfit to participate in this research due to extremely poor health, (3) reside outside the geographical range that can be visited by the respective medical institution, (4) are already receiving hospice service, or (5) are aged below 19 years.

## ***2) Caregivers***

Exclusion criteria for family caregivers are as follows: a person who (1) cannot speak, understand, or read Korean, (2) is judged by a medical doctor to be unfit to participate in this research due to extremely poor health, or (3) are aged below 19 years.

## **6. Sample size calculation**

The number of samples for the home-based program required in this study is based on a dichotomous variable, which is the primary endpoint, to secure enough patients for a stable and sufficient power. The primary endpoint of this study is the unplanned hospitalization within six months following enrollment. This study aims to determine the differences in the effects by comparing the odds ratio based on the proportion of unplanned hospitalizations in the intervention and control groups. Although no previous intervention study with a similar design has been conducted outside of Korea, the difference in pre- and post-intervention changes between the intervention and control groups should be approximately 20% (20% less in the intervention group) based on the literature review. The number of institutions in both groups is three. The parameters will be estimated using a generalized estimation equation (GEE) to compensate for the cluster effects of the study participants. The comparisons between the two groups will be analyzed using a logistic regression model, which is used to compare the effects of dichotomous outcome variables while considering other confounding variables. Therefore, a power of 80%, a significance level of 0.05 to control for type 1 error, and a 20% difference in the number of unplanned hospitalizations by intervention was used to calculate the sample size. For a ratio of 1:1 for participants in each group, the minimal sample size should be 396 patients

in total, including 198 patients for three clusters in the intervention groups and 198 patients for three clusters in the control group (assuming within-cluster coefficient=0.015).

Within-cluster coefficient (Intraclass correlation coefficient, ICC) was estimated using the analysis of variance (ANOVA) estimation method according to similar previous studies. The calculation formula is as follows (Sheng et al., 2012; Chen et al., 2015)

In the formula, 
$$n_A = \frac{1}{k-1}(N - \sum n_i^2/N) \quad MSB = \frac{1}{k-1}(\sum Z_i^2/n_i - (\sum Z_i)^2/N)$$

$$MSW = \frac{1}{N-k}(\sum Z_i - \sum Z_i^2/n_i)$$
  $k$  is the number of cluster and  $N$  is the total number of study participants.  $n_i$  and  $Z_i$  are the number of participants in group  $i$  and number of patients with endpoints in group  $i$ , respectively. Incidence rates by group were extracted from a study by Chen et al. (2015) and applied in the present study.

| k | N   | $n_1, n_2$ | $Z_1, Z_2$ | $n_A$ | MSB     | MSW      | ICC      |
|---|-----|------------|------------|-------|---------|----------|----------|
| 6 | 396 | 198,198    | 40,20      | 39.6  | 0.20202 | 0.127946 | >0.01441 |

| Power   | Sample size | # of cluster | Allocation | Average Cluster size | Effect size | ICC   | Alpha |
|---------|-------------|--------------|------------|----------------------|-------------|-------|-------|
| 0.72584 | 264         | 4            | ri(1)      | 66                   | 0.2         | 0.01  | 0.05  |
| 0.66263 | 264         | 4            | ri(1)      | 66                   | 0.2         | 0.015 | 0.05  |
| 0.5826  | 264         | 4            | ri(1)      | 66                   | 0.2         | 0.02  | 0.05  |
| 0.72584 | 264         | 4            | ri(1)      | 66                   | 0.2         | 0.01  | 0.05  |
| 0.83007 | 396         | 6            | ri(1)      | 66                   | 0.2         | 0.015 | 0.05  |
| 0.75675 | 396         | 6            | ri(1)      | 66                   | 0.2         | 0.02  | 0.05  |
| 0.88014 | 396         | 6            | ri(1)      | 66                   | 0.2         | 0.01  | 0.05  |
| 0.83007 | 396         | 6            | ri(1)      | 66                   | 0.2         | 0.015 | 0.05  |
| 0.8658  | 528         | 8            | ri(1)      | 66                   | 0.2         | 0.02  | 0.05  |
| 0.95162 | 528         | 8            | ri(1)      | 66                   | 0.2         | 0.01  | 0.05  |
| 0.92004 | 528         | 8            | ri(1)      | 66                   | 0.2         | 0.015 | 0.05  |
| 0.92905 | 660         | 10           | ri(1)      | 66                   | 0.2         | 0.02  | 0.05  |

ICC: Intraclass correlation coefficient

ri(1): The ratio of allocation for the intervention and control groups = 1:1

- Assuming a maximum dropout rate of 15% in each institution, the final number of enrolled study participants should be 57 for each institution, totaling 342 participants. The expected minimum power is 78.8% (PASS 2022, v22.0.2)
- Three institutions will participate in the intervention group (Seoul National University Hospital, Chung-Ang University Hospital, and Dongguk University Ilsan Hospital) and control group (Kyunghee University Hospital, Bundang CHA Hospital, and Bundang Seoul University Hospital). With a total of 396 expected participants, there will be sufficient power to test the differences in the effects.

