|                               | 
unscheduled hospitalization within 6 months of enrollment in the study. The study aims to reveal the difference in the effectiveness of the HBMC program by examining the odds ratio based on the proportion of unscheduled hospitalizations in the intervention and control groups. Although no previous study using an intervention with a similar design has been conducted overseas, the difference between the intervention and control groups can be expected to be approximately 20% (20% lower in the HBMC group) based on the literature review. The number of institutions in each group will be 3. The parameters will be estimated using generalized estimating equations (GEE) to consider the cluster effect of the participants at each institution. The two groups will be compared using a logistic regression model, a model of comparison of the dichotomous outcome variable. Considering the above analysis method and the assumptions of the power of 80%, a significance level of 0.05 to control type I error, a 20% change in the number of unscheduled hospitalizations before and after the intervention (20% lower in the HBMC group), and 1:1 ratio of participants between the intervention and control groups, the minimum sample size should be 198 in the intervention group and 198 in the control group, totaling 396 participants (assuming within-cluster coefficient of 0.015). Assuming a maximum dropout rate of 15%, the final number of participants to be recruited is approximately 57 for each cluster, and a total of 342 participants are expected to be recruited. The expected minimum power is 78.8% (PASS 2022, v.22.0.2).
 
- Three institutions (i.e., Seoul National University Hospital, Chung-Ang University Hospital, and Dongguk University Ilsan Hospital) will participate as the intervention institutions, and three institutions (i.e., Kyung Hee University Hospital, Cha University Bundang Medical Center, and Seoul National University Bundang Hospital) will participate as the control institutions.
 |

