| Efficacy Assessment | 
1. Data Collection
 
1) Questionnaire
 
 
- Patients and guardians in both the intervention and control groups will complete a questionnaire at the time of participant registration.
 
- Participants in the intervention and control groups will complete a follow-up questionnaire 3 months after registration.
 
- Participants in the intervention group will complete an additional questionnaire 6 months after registration. In the case of the control group, only those who will provide consent to participate in the additional questionnaire at 3 months will complete the additional questionnaire at 6 months.
 
 
2) Medical Records Investigation
 
 
- Medical records at medical institutions will be investigated at 3, 6, and 12 months after the patient's registration for hospitalization (number and dates of hospitalizations), critical care use (date of ICU admission, date of ventilator support, and number of CPR attempts), and emergency room use (number of emergency room visits) at each time point.
 
- In the case of death at 3, 6, and 12 months after registration, the deceased patient's use of medical services (hospitalization, critical care use, and emergency room use) within one month of their death will be investigated.
 
 
3) Secondary Data Linkage
 
 
- For patients who will provide consent to secondary data linkages, the hospitalizations, medical expenses, death, type of end-of-life medical services used, and the use of emergency room, critical care, and hospice between the time of registration and 12 months will be investigated when all patients have been enrolled for 12 months or longer.
 
- Death, information related to hospice use, and the type of end-of-life medical services used will be investigated when all patients have been enrolled for 18 months or longer.
 
- For patients who will consent to secondary data linkages, whether legal forms for life-sustaining treatments (e.g., advance directives and physician orders for life-sustaining treatment) have been completed and by whom will be investigated at 12 and 18 months of enrollment when all patients have been enrolled for 12 and 18 months or longer, respectively.
 
 |

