### ***4) Statistical analysis***

Definition of home-based medical service intervention group and study dropouts: Patients who provided informed consent to the selected home-based medical service intervention institutions and control group institutions are defined as the intervention group and control group, respectively. Based on the principle of group classification by intention-to-treat (ITT) that only considers the initial classification of intervention, omission of home-based medical service is still defined as the intervention group, which causes a bias that reduces the effects in the treatment group. Despite the study's design to conservatively estimate the effects in the treatment group, if significant differences are observed in the results among patients who withdraw consent or dropout during follow-up, data up to the point of withdrawal of consent or dropout will be used. Dropout rates will be analyzed and reported for each group.

The mean proportion of unplanned hospitalization will be compared between the intervention and control groups for the primary outcome. The mean of continuous variables and a fraction of dichotomous variables for each item in domains one to five will be compared between the two groups for the secondary outcome. A generalized estimation equation will be used to evaluate intra-group correlations to compensate for clusters of patients in the participating institutions. Survival after enrollment will be compared using the Kaplan-Meier curve and Cox proportional hazard model.

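### The assumed 20% effect is partly worded as a before-after change although sizing, endpoint and test are post-enrolment only, and no pre-enrolment admissions are collected to adjust six non-randomised hospitals

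*Protocol*

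**What the plan says.** The protocol words the 20% effect in two ways.

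- **As a before-after change.** Section 6 expects that "the difference in pre- and post-intervention changes between the intervention and control groups should be approximately 20% (20% less in the intervention group". The overview (Number of Study Participants) assumes "a 20% change in the number of unscheduled hospitalizations before and after the intervention (20% lower in the HBMC group".
- **As a plain difference between arms.** Section 6 goes on to say that "a 20% difference in the number of unplanned hospitalizations by intervention was used to calculate the sample size". The overview first says that "the difference between the intervention and control groups can be expected to be approximately 20" per cent. The hypothesis in section 14.A is also between arms.

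Section 12.A.1 defines the primary endpoint as the proportion of patients with an unscheduled hospitalisation in the 6 months after enrolment. (The overview calls it a number, which is a separate inconsistency; both count from enrolment.) Section 14.B.4 states: "The mean proportion of unplanned hospitalization will be compared between the intervention and control groups for the primary outcome". The overview (Statistical Analysis) specifies a logistic GEE with correction for baseline differences, and section 6 mentions other confounders.

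On data:

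- The chart review in section 11.B records hospitalisations at 3, 6 and 12 months, each time since the previous assessment.
- Linkage begins at registration. The overview says that items such as "critical care, and hospice between the time of registration and 12 months will be investigated".
- The items taken at registration (sections 9.A.2 and 11.B) are demographics, comorbidities, cancer and treatment history, symptoms and similar. Prior admissions are not named.
- The design is non-randomised, with three hospitals per arm.

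**The concern.** A difference in change and a difference in post-enrolment proportions share the same null hypothesis only if the arms have the same unscheduled-admission risk before enrolment. Nothing in the design makes that so. The hospitals were not allocated at random. The overview also exempts control patients from the home-visit-range exclusion, while section 5.B.1 lists that exclusion without an exemption. Admissions to non-participating hospitals count towards the endpoint, so where patients live may matter.

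Two things are at stake. A reader of sections 6 and 12 cannot tell which contrast the 20% refers to. And if the HBMC hospitals already differ in unscheduled admissions, the comparison can show a benefit that is not due to HBMC, or miss one that is. Section 12.C.1 would take a figure 20% lower in the intervention group as evidence that HBMC worked. A statistical analysis plan can choose covariates, but it cannot adjust for one that the protocol does not collect.

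**Working it through.** **1. What the power table actually computes**

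Inputs from section 6: "a power of 80%, a significance level of 0.05 to control for type 1 error"; "198 patients for three clusters in the intervention groups and 198 patients for three clusters in the control group (assuming within-cluster coefficient=0.015". That is 66 patients per hospital. Sidedness and arm rates are not stated. Two-sided testing and 50% v 30% are assumptions found by back-solving from the table.

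- Design effect: DEFF = 1 + (m − 1) × ICC
- Effective patients per arm: n_e = (N/2)/DEFF
- SE of the log odds ratio: √[1/(n_e p₁(1−p₁)) + 1/(n_e p₂(1−p₂))]
- Power = Φ(|log OR|/SE − 1.96), with log OR = ln[(0.5/0.5)/(0.3/0.7)] = 0.847

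For 396 patients at ICC 0.01: DEFF = 1 + 65 × 0.01 = 1.65; n_e = 198/1.65 = 120; SE = √(1/30 + 1/25.2) = 0.270; power = Φ(3.136 − 1.96) = 0.880.

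| N | m | ICC as labelled | Stated power | Recomputed |
|---|---|---|---|---|
| 396 | 66 | 0.01 | 0.88014 | 0.88014 |
| 396 | 66 | 0.02 | 0.75675 | 0.75675 |
| 264 | 66 | 0.01 | 0.72584 | 0.72584 |
| 264 | 66 | 0.02 | 0.5826 | 0.58260 |
| 528 | 66 | 0.01 | 0.95162 | 0.95162 |
| 528 | 66 | 0.02 | 0.8658 | 0.86580 |
| 660 | 66 | 0.02 | 0.92905 | 0.92905 |
| 342 | 57 | 0.015 | 0.788 | 0.788 |
| 396 | 66 | 0.015 | 0.83007 | 0.81756 (0.83007 at ICC 0.014) |
| 264 | 66 | 0.015 | 0.66263 | 0.64809 (0.66263 at ICC 0.014) |
| 528 | 66 | 0.015 | 0.92004 | 0.91141 (0.92004 at ICC 0.014) |

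The last three rows appear to have been run at 0.014, which is a separate matter. The calculation has one period and two arms, with no pre-period and no pre/post correlation. It matches the planned test, not the before-after wording.

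**2. What a pre-existing gap could do (illustration)**

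Assumptions: control risk 50%, ICC 0.015, 396 patients, no baseline adjustment. DEFF = 1.975 and n_e = 198/1.975 = 100.25.

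No true effect, HBMC hospitals 5 points lower (50% v 45%): log OR = 0.201, SE = 0.283, ratio 0.709. Rejection = Φ(0.709 − 1.96) + Φ(−0.709 − 1.96) = 0.105 + 0.004 = 0.109.

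| Pre-existing gap | No true effect, HBMC lower: two-sided rejection | True 20-point effect, HBMC higher: power |
|---|---|---|
| 0 | 5% | 82% |
| 5 points | 11% | 57% |
| 10 points | 30% | 30% |

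For scale, ICC 0.015 at 50% gives a between-hospital SD of √(0.015 × 0.25) = 6.1 points. A 3 v 3 mean difference then has SD 6.1 × √(2/3) = 5.0 points.

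**3. Whether 396 patients would serve a change contrast**

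This takes a 20-point difference in change, with control flat at 50% and HBMC going from 50% to 30%. Per-arm variance = (1 − ICC)(v₁ + v₂ − 2ρ√(v₁v₂))/198 + ICC(v₁ + v₂ − 2c√(v₁v₂))/3, where v = p(1 − p), ρ is the within-patient correlation and c the cluster autocorrelation. The protocol gives neither ρ nor c.

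- ρ = 0, c = 0: control 0.00499, HBMC 0.00459, SE = 0.0979; power = Φ(2.04 − 1.96) = 0.53.
- ρ = 0, c = 0.8: power 0.75.
- ρ = 0.5, c = 1: power 0.98.

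So 396 patients do not guarantee 80% power for the change contrast.

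**The case against.** The strongest reply is that this is an editorial slip in an openly non-randomised trial. Much of that stands.

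- A reader might infer from section 6 that the trial was sized on a change and tested on something else, so that the sample size is wrong. The documents do not support this: the table reproduces as a post-only comparison, and sections 6 and 14.A and the overview also state a plain between-arm 20%.
- A reader might infer that no confounding control is planned. The overview and section 6 do plan correction for baseline characteristics, with no closed covariate list. This reduces confounding by measured patient mix.
- The gaps in the illustration are assumed, and no adjustment is applied. Hospital variation at ICC 0.015 is already in the design effect. A 10-point gap is about two SDs of that variation, so it presupposes systematic differences for which the protocol gives no figure. The percentages are not estimates of this trial's error rate.

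What does not fall away is the data gap. Prior unscheduled admission is the most direct baseline of the primary outcome, it appears in none of the listed data, and the design effect covers random hospital variation only. An analysis plan written later cannot supply it.

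**Conclusion.** Two limited findings hold. First, the before-after phrases in section 6 and the overview contradict the endpoint, hypothesis, test and power table; the text needs correcting, not the sample size. Second, with six non-randomised hospitals and no pre-enrolment admissions, the planned baseline correction cannot use the outcome's own baseline, so a pre-existing hospital difference may be read as an HBMC effect or conceal one.

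The real gap is unknown. The rise in rejection from 5% to about 11% or 30%, for gaps of 5 or 10 points, rests on an assumed 50% control risk, ICC 0.015 and no adjustment.

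A reader might also infer that adding prior admission as a covariate would settle the matter. It would not: in a simulation under assumed patient heterogeneity, a patient-level covariate removed only about 6% to 37% of a hospital-level gap. The hospital-level change contrast is therefore needed beside it, but only as support, since power for it is not assured.

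**What to change.** 1. In section 6 and the overview, reword the before-after phrases as an absolute between-arm difference in the 6-month proportion, and state the two arm rates used. This matters because the ICC table uses 40/198 and 20/198 (20.2% v 10.1%), whereas the power table reproduces at 50% v 30%.
2. At registration, record unscheduled hospitalisations in the 6 months before enrolment for every patient in both arms from the institution's chart, flagging the index admission of those enrolled as inpatients. Start the consented linkage 6 months before registration in both arms. Reconcile section 11.C, which describes linkage for the intervention group, with the overview, which does not restrict it.
3. Add prior unscheduled admission as a covariate in the primary GEE. Report the hospital-level pre-to-post change contrast as a supporting analysis only.

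**Cost:** one look-back item, an earlier start date in a linkage already planned, one covariate, and changes to IRB and consent wording. No extra patients or visits are needed. The records already exist, so patients already enrolled can be covered, subject to consent.

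**Limits:** outside-hospital look-back exists only for patients who consent to linkage. The linkage items in section 11.C hold no scheduled/unscheduled field, so for linked data the pre-enrolment definition matches the endpoint only approximately.

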## **14. Statistical analysis**

### **A. Hypothesis**

The intervention group will show a 20% decrease in unplanned hospitalization than the control group.

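### Section 6 powers the trial on an effect of 0.2 without printing the two proportions, and the only event rates it shows (20.2% vs 10.1%) do not fit that effect

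*Protocol*

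**What the plan says.** For the error rates, Section 6 sets "a power of 80%, a significance level of 0.05 to control for type 1 error". For the effect, it states that "a 20% difference in the number of unplanned hospitalizations by intervention was used to calculate the sample size". The two arms are to be contrasted by "comparing the odds ratio based on the proportion of unplanned hospitalizations in the intervention and control groups", through a logistic GEE, with 198 patients and three hospitals per arm and an ICC of 0.015. The 20% is attributed to a literature review. No control-arm proportion is attached to it.

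The section then derives the ICC. It says that incidence rates by group were taken from a cited cohort study "and applied in the present study". The worksheet enters 40 and 20 events among 198 and 198 patients and ends with "0.20202 | 0.127946 | >0.01441" for MSB, MSW and ICC.

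The power table below the worksheet lists effect size 0.2 and ICC values of 0.01, 0.015 and 0.02. For 396 patients at ICC 0.015 it gives 0.83007. With 57 patients per hospital (342 in all) the expected minimum power is given as 78.8%. The section closes: "With a total of 396 expected participants, there will be sufficient power to test the differences in the effects".

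Elsewhere, Section 14.A states the hypothesis as "The intervention group will show a 20% decrease in unplanned hospitalization than the control group". Section 12.C takes a 20% lower mean than in the control group as the sign of effectiveness.

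**The concern.** Power for a binary endpoint depends on both proportions. Section 6 prints neither for its power table, so the stated power cannot be checked from the text. The only rates it does print differ by 10 points. A 20-point fall from 20.2% would leave almost no events in the intervention arm. The rates behind the ICC and the effect behind the power table therefore describe two different situations, and nothing in the section links them.

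Sections 12.C and 14.A add to the doubt, because a 20% decrease can mean 20 percentage points or a fifth of the control rate. What is at stake is what the stated power can be said to cover. A reader who takes the worksheet rates as the expected rates, or the hypothesis as relative, would credit the trial with far more power than it has for those effects.

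**Working it through.** **Inputs from Section 6.** 198 per arm; 66 per hospital; ICC 0.01, 0.015 or 0.02; effect size 0.2; alpha 0.05; worksheet counts 40/198 and 20/198; 57 per hospital (171 per arm) after dropout. Sidedness is not stated; two-sided is assumed here because it reproduces the table.

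**Formula.** Wald test of the log odds ratio, in line with the planned logistic GEE:

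- DEFF = 1 + (m − 1) × ICC
- SE² = (DEFF / n per arm) × [1/(p1q1) + 1/(p2q2)], with q = 1 − p
- z = |logit p1 − logit p2| / SE
- power = Φ(z − 1.96)

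**Step 1: reproduce the table.** Take 50% vs 30%. The log odds ratio is 0.8473 and the bracket is 4 + 4.762 = 8.762. At 396 patients and ICC 0.01, DEFF = 1.65, SE = √(1.65/198 × 8.762) = 0.2702 and z = 3.136, so power = 0.88014, as printed. The other rows:

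| Patients | ICC label | Printed | At labelled ICC | At ICC 0.014 |
|---|---|---|---|---|
| 264 | 0.01 | 0.72584 | 0.72584 | |
| 264 | 0.015 | 0.66263 | 0.648 | 0.66263 |
| 264 | 0.02 | 0.5826 | 0.5826 | |
| 396 | 0.01 | 0.88014 | 0.88014 | |
| 396 | 0.015 | 0.83007 | 0.818 | 0.83007 |
| 396 | 0.02 | 0.75675 | 0.75675 | |
| 528 | 0.01 | 0.95162 | 0.95162 | |
| 528 | 0.015 | 0.92004 | 0.911 | 0.92004 |
| 528 | 0.02 | 0.8658 | 0.8658 | |
| 660 | 0.02 | 0.92905 | 0.92905 | |

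The protocol prints two of these rows twice, which makes twelve. The eight at ICC 0.01 and 0.02 match to the printed digits. The four labelled 0.015 match only at 0.014.

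For 342 patients, DEFF = 1 + 56 × 0.015 = 1.84 and power = 0.788, as stated. That figure does use 0.015; at 0.014 it would be 0.800. The table and the 78.8% thus rest on different ICC values under the same label.

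70% vs 50% gives identical power throughout, so the table cannot show which pair was used.

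**Step 2: how far the control rate matters for a 20-point difference.** At 396 patients and ICC 0.015:

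| Rates | Power |
|---|---|
| 30% vs 10% | 0.924 |
| 40% vs 20% | 0.861 |
| 50% vs 30% | 0.818 |
| 60% vs 40% | 0.803 |
| 70% vs 50% | 0.818 |
| 80% vs 60% | 0.861 |

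**Step 3: the worksheet's rates.** First, the ICC. With n_A = (396 − 2 × 198²/396)/5 = 39.6, the ICC is (0.20202 − 0.127946) / (0.20202 + 38.6 × 0.127946) = 0.01441, as printed. The 40 and 20 events are therefore what enter the ICC.

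Now the power at those rates. The log odds ratio is ln[(40 × 178)/(158 × 20)] = 0.8123 and the bracket is 6.203 + 11.012 = 17.216.

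- 396 patients, ICC 0.015: DEFF = 1.975, SE = √(1.975/198 × 17.216) = 0.4144, z = 1.960, power 0.500. At ICC 0.01 it is 0.573; at 0.02, 0.443.
- 342 patients, ICC 0.015: SE = √(1.84/171 × 17.216) = 0.4304, z = 1.887, power 0.471.

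A pooled two-proportion formula gives much the same: 0.514 and 0.484.

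**Step 4: 20% read as a relative reduction.** At 396 patients and ICC 0.015, power is 0.11 for 20% to 16%, 0.29 for 50% to 40% and 0.53 for 70% to 56%. These control rates are illustrations, because the protocol fixes none.

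**The case against.** The best defence is that the worksheet and the power table serve different purposes. The sentence about the cohort's rates closes the ICC paragraph, the counts appear only in the ICC worksheet, and the 20% effect has its own stated source in the literature review. The protocol never says that it expects 20% vs 10%. That stands. A reader might infer that the trial has only 50% power at its own planning rates, but the text does not go so far. The 50% holds only if the worksheet rates are also what the trial expects.

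Second, if effect size 0.2 means 20 points, power at 396 patients is at least about 80% at every control rate tried in step 2. The closing sentence on power is then correct, and a qualification is enough. This stands too.

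Third, 50% vs 30% is recovered from the printed figures, not stated, and 70% vs 50% fits as well. The sponsor has to say which pair was used.

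Fourth, Section 12.C is a rule of interpretation, and 14.A is loose wording that could mean points. A reader might see a separate, smaller design effect there, but what the documents show is an ambiguity.

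None of this supplies the missing proportions, reconciles a 10-point difference with an effect of 0.2, or explains the rows labelled 0.015.

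**Conclusion.** The point holds in this form. Section 6 does not state the proportions behind its power table, and the only event rates that it prints, which drive its ICC, do not fit the effect size. Among the effects described, power of about 80% or more at 396 patients is limited to an absolute 20-point difference. It is about 50% at 20.2% vs 10.1% (47% at 342), roughly 30 points below the stated figures. The rows labelled ICC 0.015 are 0.9 to 1.5 points too high for that label.

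This rests on the Wald log-odds-ratio method, two-sided 0.05 and equal cluster sizes. The method is well supported, since it returns eight of the twelve rows and the 78.8% exactly. A reader might conclude that the sample size is wrong or must grow; that does not follow, because which rates the trial expects is not settled by the document.

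**What to change.** In Section 6 and the synopsis:

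- State the control and intervention proportions actually used for the power table, and reconcile them with the rates used for the ICC.
- Correct the rows labelled ICC 0.015 to 0.648, 0.818 (both entries) and 0.911, or relabel them 0.014.
- State that the power applies to an absolute 20-point difference, and add the power at 20.2% vs 10.1%: about 50% at 396 patients and 47% at 342.
- Qualify the closing sentence on sufficient power to match.

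In Sections 6, 12.C and 14.A, say whether 20% is absolute or relative. If relative is meant, give the power at the stated control rate; step 4 shows how strongly it depends on that rate.

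The cost is protocol wording and a more guarded power statement. No patients are added.
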